## Statistical methods

### Statistical methods for primary and secondary outcomes {20a}

Data analysis will be performed using descriptive statistical analysis and inferential statistics. The sample data will be presented by frequencies or percentages, means ± standard deviation or median and interquartile range, and graphics. The IBM® SPSS® Statistics for Windows, version 26 software (IBM Corp., Armonk, NY, USA) will be used for all statistical analyses.

For the evaluation of primary outcomes, 3 × 2 analyses of variance for repeated measurements (ANOVA) will be used: For evaluating the long-term changes in CRP and cortisol (hair and saliva), 2-factorial ANOVAs with the factors “time point” (T0, T1, T2) and “group” (IG or CG) will be conducted. For the evaluation of the acute effects of the training intervention, further ANOVAs with the factors “time point” (before, after, and 20 min after the training) and “training number” (second or seventh training) will be calculated. For the evaluation of further secondary outcomes, comparable analyses will be conducted.

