### Objectives {7}

The aim of the study is to investigate the acute and chronic physiological stress-related health benefits of a cycling intervention in older adults. The analysis of the patho-physiological parameters involves two parts: first, the effects of an 8-week cycling exercise training program on general cortisol and CRP levels and, second, the investigation of the acute physiological effects of a cycling training on cortisol and sAA as stress-related health outcomes. We hypothesize that the cycling intervention will have stress-reducing and health benefits in the long term. Furthermore, we hypothesize that the acute cycling training will be a physical stressor, which will be perceived as a stressor associated with anxiety (leading to HPA axis responses) at the beginning of the training. We expect that at the end of the intervention, the training will be a physical stressor only. This reduced acute stress should lead to a general reduction of cortisol levels.

Therefore, as a primary outcome, the following hypotheses will be tested:
Cortisol (measured in the saliva at bedtime and in the hair) will decrease significantly after the intervention in comparison with the control group.

Our secondary hypothesis is that the acute effects of a cycling training on salivary cortisol levels (as a marker for HPA axis activity) will be compared between the beginning and the end of the intervention and will be lower after the seventh than after the second lesson.

Furthermore, we will explore the following parameters to understand better the psychological adaptations to the cycling training: changes in fear of falling and perceived stress before and after the intervention. Moreover, the acute effects of the training on salivary alpha amylase, perceived stress, and anxiety will be investigated.

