#### Intervention description {11a}

SiFAr-Stress is an additional part of the SiFAr study following the time course of the main study. SiFAr consists of a practical and a theoretical part within 2 years. In the first year, the IG will participate in the multicomponent exercise program including cycling with a duration of 3 months, whereas the CG will take part in the theoretical course concerning bicycle-relevant lectures. Participants will be recruited from March to July. Both groups (IG + CG) will be tested for the performance in the cycling course and for functional and psychological parameters at T0 (before the intervention), T1 (after the 3-month intervention), and at 6 to 9-month follow-up (T2). To analyze stress- and health-related physiological parameters, biological specimen saliva, hair, and capillary blood will be collected. These patho-biological specimens will be collected during the intervention period to compare the change of different parameters during the intervention. The time points for biological specimen collection are identical as for functional and psychological parameters at T0, T1, and T2. The change of the concentration of stress hormone cortisol in the saliva specimen will be measured at T0 and T1. After completion of the intervention, all participants will be observed and tested as follow-up after 6 to 9 months.

Furthermore, short-term changes of cortisol concentration in the saliva specimens will be monitored for an acute-phase situation (prior, immediately after, and 20 min after the training session). The acute-phase situation will be determined twice during the training period, at the second and the second last training lesson. Therefore, the influence of the exercise training on the acute cortisol response in saliva will be determined.

In addition, hair specimens will be analyzed compared to longitudinal cortisol concentration. The inflammatory marker CRP will be analyzed in the capillary blood. The change in CRP concentration in the blood allows conclusions on inflammatory processes in the body.

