### Outcomes {12}

The primary outcome is the change in cortisol and between the beginning of the intervention (T0) and after the intervention (T1). As secondary outcomes, the mean changes in fear of falling (FES-I) and psychological parameters (sAA, CRP, stress (PSS)) over a period of 3 months (after the intervention) and after a follow-up period of 6 to 9 months will be analyzed. Furthermore, the acute effects on cortisol levels during a session at the beginning and at the end of the training intervention (Tr1 and Tr7) will be assessed.

Cycling accidents during the intervention period present a potential risk for the participants and therefore might be a potential harm outcome.

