### Methods in analysis to handle protocol non-adherence and any statistical methods to handle missing data {20c}

Non-adherent participants will be excluded from the analysis. Attendance of the participants will be monitored weekly to administer adherence to the intervention. If participants attended at least 6 of the lessons, they are considered as “adherent” to the intervention.

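### The primary outcome is the T0-to-T1 change in cortisol, but the analysis named for it is a T0/T1/T2 repeated-measures ANOVA in which no F-test isolates T1

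*Protocol article*

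**What the plan says.** - **Primary outcome** (Outcomes {12}): "The primary outcome is the change in cortisol and between the beginning of the intervention (T0) and after the intervention (T1". T2 enters that section only in the next sentence, on secondary outcomes, whose changes "over a period of 3 months (after the intervention) and after a follow-up period of 6 to 9 months will be analyzed".
- **Hypothesis** (Objectives {7}): cortisol, in bedtime saliva and in hair, "will decrease significantly after the intervention in comparison with the control group".
- **Analysis** (Statistical methods {20a}): for the primary outcomes, 3 × 2 "analyses of variance for repeated measurements (ANOVA) will be used"; for cortisol and CRP, "2-factorial ANOVAs with the factors “time point” (T0, T1, T2) and “group” (IG or CG) will be conducted". The section does not say which F-test decides and names no T0–T1 contrast. CRP, a secondary outcome under {12}, is handled in the same sentence as cortisol. SPSS "version 26 software (IBM Corp., Armonk, NY, USA) will be used for all statistical analyses".
- **Sample size** {14}: f = 0.3, α = 0.05, power 0.80, three time points and 1:1 allocation give about 111, raised to 140 for 20% drop-out. The text calls this a comparison between the two groups.
- **Non-adherence and missing data** {20c}: "Non-adherent participants will be excluded from the analysis". No method for a missing visit is given there.

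**The concern.** The outcome and the test answer different questions. The outcome asks whether the groups differ in change from before to just after the intervention. The ANOVA asks whether the groups differ anywhere in their profile over three visits, the last of them 6 to 9 months later.

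The trial could therefore report a positive primary analysis on the strength of the follow-up visit with nothing shown at T1. Because three F-tests come out of the model and none is designated, it is also open which one decides.

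A second consequence is inferred, not stated. Conventional repeated-measures ANOVA in SPSS keeps only participants with all three values, so a participant with valid T0 and T1 samples but no T2 sample would be lost from the test of a T0–T1 outcome.

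**Working it through.** **1. The plan's own figure.** Inputs from Sample size {14}: f = 0.3 (f² = 0.09), α = 0.05, power 0.80, two groups, three time points.
- Group-by-time interaction, multivariate form: λ = N f² = 111 × 0.09 = 9.99, df 2 and N − 3 = 108, power 0.803. N = 111 is reproduced.
- Interaction, univariate form with λ = f²(N − 2) = 109 × 0.09 = 9.81, df 2 and 2(N − 2) = 218: also N = 111. With the alternative convention λ = 3Nf²/(1 − ρ), N would be 20 at ρ = 0.5.
- Group main effect, λ = 3Nf²/(1 + 2ρ), df 1 and N − 2: N = 61 at ρ = 0.5 and at most 90 (ρ = 1). This does not give 111.
- Drop-out: 111/0.8 = 138.75, so 139 against the stated 140; 140 × 0.8 = 112.

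So, despite the wording about a comparison between groups, the number fits the 2-df interaction.

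**2. What each F-test tests.** Let δ1 and δ2 be the true group differences (SD units) at T1 and T2. At T0 the difference is zero by randomisation, since {16c} places randomisation after the baseline assessments.
- Time main effect: no group comparison.
- Group main effect: (0 + δ1 + δ2)/3, so T0 dilutes it and T2 counts as much as T1.
- Group-by-time interaction: null δ1 = δ2 = 0. Under compound symmetry with correlation r, λ = (N/4) × 2(δ1² − δ1δ2 + δ2²)/[3(1 − r)]. This is symmetric in δ1 and δ2, so an effect at T2 alone gives the same power as an equal effect at T1 alone.

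Example: N = 111, r = 0.5, δ1 = 0, δ2 = 0.537 SD (the size at which a T0–T1 change contrast would have 80% power if the effect were at T1). The interaction rejects about 83% of the time; the T0–T1 contrast rejects 5%.

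**3. Power, same people in each analysis.** Assumptions, not in the documents: δ1 = 0.4 SD, δ2 = c × δ1, compound symmetry. N = 112. Then (N/4)δ1² = 28 × 0.16 = 4.48.
- ANCOVA at T1 with T0 as covariate: λ = 4.48/(1 − r²), df 1 and 109.
- T0–T1 change contrast: λ = 4.48/[2(1 − r)], df 1 and 110.
- Interaction: λ = 4.48 × 2(1 − c + c²)/[3(1 − r)], df 2 and 220.

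| r | ANCOVA: λ, power | Change: λ, power | Interaction, c = 0 or 1: λ, power | Interaction, c = 0.5: λ, power |
|---|---|---|---|---|
| 0.3 | 4.92, 59% | 3.20, 43% | 4.27, 43% | 3.20, 34% |
| 0.5 | 5.97, 68% | 4.48, 55% | 5.97, 58% | 4.48, 45% |
| 0.7 | 8.78, 84% | 7.47, 77% | 9.96, 81% | 7.47, 68% |

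The ratio of the interaction's λ to that of the change contrast is (4/3)(1 − c + c²). It is 4/3 when the effect is fully kept or fully gone at T2, which roughly pays for the second degree of freedom, and 1 when half is kept, which does not. At c = 0.25 or 0.75 the interaction has 36/49/72%, still below the change contrast.

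**The case against.** The strongest reply has four parts.

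- **An omnibus test followed by contrasts is ordinary practice, and a condensed article may leave the contrast to an analysis plan.** This would carry weight if {20a} were silent. It is not: it names the test for the primary outcomes, and that test includes a visit outside the primary window.
- **The interaction is a valid test in a randomised trial, and treating T0 as an outcome is not an error.** True. Baseline adjustment is a gain in efficiency. The defect is the mismatch with T1.
- **Power is not generally lost.** This stands. A reader might infer that including T2 always costs power, but against the plain change contrast on the same people it does so only under partial retention. Setting ANCOVA on everyone seen at T1 against the interaction on three-visit completers would widen the gap, but would mix baseline adjustment with an assumed T2 loss. The low power of the group main effect is no measure of harm either, because the sample size points to the interaction as the intended test.
- **Loss of people missing T2 is budgeted.** This also stands as to number: 140 leaves 112 after 20% drop-out. What remains is the discarding of valid T0–T1 pairs and the selection that goes with it.

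A reader might also take the sentence in Intervention description {11a}, "The change of the concentration of stress hormone cortisol in the saliva specimen will be measured at T0 and T1", to mean that a three-level saliva analysis cannot be run. The documents do not support this. The sentence before it sets specimen collection at T0, T1 and T2, and the stress-system assessment section and Table 2 do the same. It is loose wording only.

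**Conclusion.** The point holds as a mismatch between the primary outcome and the test assigned to it. It follows from {12} and {20a} side by side and from what the F-tests compare; it needs no assumption about effect size or correlation. A significant group-by-time interaction would not establish a T0–T1 reduction relative to control.

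The power figures are secondary and rest on assumptions (0.4 SD at T1, compound symmetry, r from 0.3 to 0.7, 112 in each analysis). In that range ANCOVA at T1 has 59/68/84% against 34–43/45–58/68–81% for the interaction. Part of that difference is baseline adjustment, not the removal of T2. The complete-case loss is a sound inference from the method and software, but the article does not state it.

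**What to change.** - In {20a}, for each cortisol marker (bedtime saliva and hair), make the IG–CG difference at T1 adjusted for the T0 value of that marker the single primary test. Use either ANCOVA on T1, or a linear mixed model for T1 and T2 with T0 as covariate and the T1 contrast as the test. The mixed model keeps participants who have T1 but not T2.
- Report T2 as a secondary contrast, and list CRP with the secondary outcomes, as in {12}.
- Restate {14} for the T1 contrast. If the same noncentrality were kept (λ = 0.09N), a 1-df test would need N = 90 for 80% power, and N = 111 would give 0.880 instead of 0.803. But f = 0.3 was set for a three-visit ANOVA, so the effect should be restated as a T1 difference with an assumed T0–T1 correlation.
- Align the saliva sentence in {11a} with T0, T1 and T2.

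The cost is wording in the protocol and analysis plan, with the same data and software. It should be done before outcomes are compared by group.

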### Interim analyses {21b}

Not applicable

### Methods for additional analyses (e.g., subgroup analyses) {20b}

Not applicable

### Methods in analysis to handle protocol non-adherence and any statistical methods to handle missing data {20c}

Non-adherent participants will be excluded from the analysis. Attendance of the participants will be monitored weekly to administer adherence to the intervention. If participants attended at least 6 of the lessons, they are considered as “adherent” to the intervention.

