### Criteria for discontinuing or modifying allocated interventions {11b}

Criteria for discontinuing the intervention for a given participant are adverse event–like accident with severe injuries (e.g., fractures), serious illness, and quarantine (coronavirus) preventing to participate in the intervention.

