### Implementation {16c}

After the assignment of the informed consent and the baseline assessments by trained study staff, randomization is performed by enrolling participants in concealed randomization lists by a separate person that only receives the information necessary for stratification.

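### The only stated analysis set drops randomised participants who attended fewer than 6 lessons, so randomisation no longer protects the primary comparison of cortisol change

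*Protocol article*

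**What the plan says.** Section {20c} of the protocol article contains one rule on the analysis set: "Non-adherent participants will be excluded from the analysis". It defines adherence by attendance: "If participants attended at least 6 of the lessons, they are considered as “adherent” to the intervention".

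The sections around it add the following.

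- **Timing.** Implementation {16c}: "After the assignment of the informed consent and the baseline assessments by trained study staff, randomization is performed". Attendance is therefore observed only after allocation.
- **Two different activities.** Under Intervention description {11a} the intervention group has practical cycling lessons, with acute sampling "at the second and the second last training lesson". Elsewhere the later of these two is called the seventh lesson, which implies 8 lessons. In the other arm, "the CG will take part in the theoretical course concerning bicycle-relevant lectures". No number of lectures and no separate attendance threshold is given.
- **Reasons for stopping.** Section {11b} lists "accident with severe injuries (e.g., fractures), serious illness, and quarantine (coronavirus) preventing to participate in the intervention".
- **No other analysis set.** Statistical methods {20a} names none, and additional analyses {20b} are marked as not applicable. The only other exclusions, in the Discussion, concern medication and outlying cortisol values.

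**The concern.** The primary hypothesis under Objectives {7} is a comparison between randomised groups: cortisol should fall more with cycling than in the control group. Randomisation makes the groups comparable when everyone is analysed as assigned. Selecting on attendance afterwards gives up that protection, because attending is itself a response to the assigned course.

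The article gives reasons to expect that attendance could relate to outcome. Objectives {7} expects early training to be a stressor associated with anxiety. The stopping reasons in {11b} include severe injury and serious illness. If people who miss lessons for such reasons would have had a less favourable cortisol change, removing them from the cycling arm makes that arm look better than it is.

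The rule may also work differently in the two arms. If the 6 lessons refer only to cycling, exclusion is one-sided. If they also cover the lectures, the same count selects on different activities.

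This is not a detail left to a statistical analysis plan. The article fixes the rule: a plan that followed it would carry the problem forward, and a plan that analysed everyone would contradict it.

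**Working it through.** **1. The plan's own sample size.** Inputs from Sample size {14}: f = 0.3, alpha 0.05, power 0.80, two groups, three time points, 20% drop-out. Take the group-by-time F test with 2 and 2(N − 2) degrees of freedom.

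- With noncentrality f²(N − 2), the smallest N is 111 (power 0.802). This matches the stated figure. With noncentrality f²N it is 109.
- 111 / 0.8 = 138.75, so 139; the plan takes 140.
- Expected completers: 140 × 0.8 = 112, or 56 per arm. The margin over 111 is 1.

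**2. Room for adherence exclusions.** Assume that these exclusions come on top of the 20% drop-out. Two of them already give 112 − 2 = 110, below 111. The article gives no non-adherence rate, so 10% to 40% is assumed. Power uses noncentrality f²N (f²(N − 2) gives about 0.01 less) and ignores the small loss from unequal arms.

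| Excluded | Cycling arm only: N = 56(2 − q) | Power | Both arms: N = 112(1 − q) | Power |
|---|---|---|---|---|
| 0% | 112 | 0.81 | 112 | 0.81 |
| 10% | 106 | 0.79 | 101 | 0.77 |
| 20% | 101 | 0.77 | 90 | 0.71 |
| 30% | 95 | 0.74 | 78 | 0.65 |
| 40% | 90 | 0.71 | 67 | 0.58 |

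**3. What must be true for bias.** The primary outcome is change from T0 to T1, analysed by group and time point. An excluded person leaves at every time point. If non-adherers have a cortisol gap that is the same at T0 and T1, it cancels in the change. Bias requires a different *change* in non-adherers.

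**4. Illustrative size.** Assumptions: no true effect, 56 per arm before exclusion, and exclusion in the cycling arm only. A share q is excluded, and r is the correlation between the tendency to attend and a favourable cortisol change. Change is in SD units and compared between two groups; this simplifies the planned three-time-point ANOVA.

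- k = φ(z_q) / (1 − q), where z_q is the q-quantile of the standard normal
- bias b = r × k
- SE = √[ (1 − r²k(k − z_q)) / (56(1 − q)) + 1/56 ]
- type I error = P(|Z + b/SE| > 1.96)

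Worked case, q = 20% and r = 0.3: k = 0.350, b = 0.3 × 0.350 = 0.105, SE = 0.198, type I error 8.3%.

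| q | r = 0.1 | r = 0.3 | r = 0.5 |
|---|---|---|---|
| 10% | 0.019 SD (5.1%) | 0.058 SD (6.1%) | 0.097 SD (8.1%) |
| 20% | 0.035 SD (5.4%) | 0.105 SD (8.3%) | 0.175 SD (14.7%) |
| 30% | 0.050 SD (5.7%) | 0.149 SD (11.2%) | 0.248 SD (23.6%) |

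At r = 0 there is no bias. A negative r reverses the sign. Similar selection in both arms would partly cancel it.

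**5. A case with the opposite sign.** Suppose non-adherers start 0.5 SD higher and the T0–T1 correlation is 0.5. By regression to the mean their T1 gap is 0.5 × 0.5 = 0.25 SD, so their cortisol falls 0.25 SD more than that of the adherers. Removing 25% of the cycling arm then shifts the change contrast by 0.25 × 0.25 = 0.0625 SD *against* cycling.

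**The case against.** A reader might infer that the rule is bound to favour cycling, because it removes the most stressed members of that arm. The documents do not support this. Higher stress alone is not enough, since a stable gap cancels in the change, and step 5 shows that the sign can reverse. Nor do all participants enter because they feel insecure: Eligibility criteria {10} gives insecurity as one of three alternatives, beside being new to the e-bike and returning to cycling.

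A reader might also take the power loss as certain. The article does not define drop-out, so people who stop attending may already be counted in the 20%. Some who are injured, ill or in quarantine might give no T1 sample whatever the analysis set, so not all of that loss comes from this rule.

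Finally, one could say that the effect in people who actually take the course is of interest. It is, as a supporting question. But the rule is stated without qualification and is not labelled per-protocol or secondary.

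These points limit what can be said about direction and size. They do not touch the central one: the article contains no analysis of participants as randomised.

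**Conclusion.** The point stands as a defect in the stated analysis set and should be corrected before analysis. That the only stated set depends on post-randomisation attendance rests on explicit text and needs no assumption.

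Bias is possible and, on the article's own account of anxiety and of reasons for stopping, plausibly favours cycling. That reading depends on non-attenders having had a less favourable cortisol change, which the article does not show. The type I error figures of 5.1% to 23.6% are illustrative: they rest on assumed exclusion rates, an assumed positive correlation and exclusion in one arm. They are not estimates for this trial.

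It would also go too far to say that the trial could support no causal statement at all. How far the comparison is compromised depends on how many are excluded and how selectively, and neither is known. The sample size consequence is conditional in the same way: a margin of one participant leaves no room if non-adherence is not already within the drop-out allowance.

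**What to change.** Replace the exclusion sentence in {20c} with wording such as: *The primary analysis includes all randomised participants in the group to which they were assigned, regardless of attendance, using all available cortisol data.* Then:

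- keep the set with at least 6 lessons as a labelled sensitivity analysis, and state for each arm what counts as adherent, including the number of control lectures;
- state that T1 and T2 samples are still sought from people who stop attending;
- state whether the 20% drop-out includes non-adherence.

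The cost is a few sentences, plus the effort of sampling people who no longer attend. The estimated effect may be slightly diluted by non-attenders. N = 140 need not change: 112 completers give power of about 0.81 for f = 0.3, taking the same f with no dilution.
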